## **2.0 Problem statement and justification**

Although it is feasible to implement CRP in poorly resourced areas, Malawi has not championed the intervention. Additionally, it is known that the treatment guidelines of CVD in Malawi do not clearly incorporate CR as an integral component of the management process. Therefore, there is need to conduct a pilot CR intervention to inform the feasibility and importance of the strategy. The outcomes of this pilot program will also sensitize the healthcare providers and managers on the need to incorporate CRP in the CVD management guidelines for Malawi. In addition, the findings will inform the strategic planning and implementation of the CR intervention at QECH, which would be scaled up to other hospitals; thereby increasing accessibility.

## **3.0 Objectives**

### **3.1 Broad objective**

The overall aim of this study is to carry out a pilot study to determine the impact of cardiovascular rehabilitation among patients with a diagnosis of Congestive Heart Failure (CHF).

### 3.2 Specific Objectives

1. To describe the improvements in cardiovascular function among patients with CHF following administration of CR
2. To describe the frequency of hospitalization among patients diagnosed with CHF
3. To describe the challenges that may be associated with establishment of a CRP at QECH

## 4.0 Methodology

### 4.1 Design

The study shall use a prospective open label clinical trial design, and quantitative methods will be employed.

### 4.2 Study site

The study will be conducted at QECH, in Physiotherapy department

### 4.3 Study population

Patients with CHF, who come for follow up medical care at the QECH chest clinic at QECH, shall constitute the target population.

#### 4.31 Inclusion criteria

- a. Men and women 18 years and above with a diagnosis of CHF at discharge from hospital, confirmed with an echocardiogram
- b. Being residents of Blantyre City and its immediate surrounding areas
- c. Willing to provide written informed consent and willing to return for follow up
- d. Being able to participate in physical activity for cardiac rehabilitation

#### **4.32 Exclusion criteria**

- a. Failure to provide informed consent form
- b. Not willing to return for follow up visits
- c. Physical impairment that would affect participation in physical activity
- d. Coming from outside Blantyre
- e. Patients classified as high risk for cardiac events during exertion

#### **4.4 Sample size, sampling method and study period**

This study will enrol patients with CCF, who will come for medical check-up during the eight-week period of study participants' enrolment. According to the medical register book, there is a varying number of CCF patients who come for the clinic each week. For instance, out of a total of 53, 212 and 130 patients who came to receive cardiac or respiratory related medical care through this chest clinic in January, February and March, 19, 45 and 28 patients had CCF respectively. The clinic was temporarily shut down between April and September due to COVID-19 pandemic, and it recently resumed its services. However, out of 77 and 116 patients who came to this chest clinic in October and November after resumption of the clinic's services this year, 5 and 13 patients had CCF. This shows a drastic reduction in the number of cases coming for medical care; nevertheless, the numbers have reduced as a strategy to avoid congestion in the clinic and protect the patients from contracting or spreading the SARS-2 virus that causes COVID-19. It is expected that the number of patients coming for this clinic will remain low until Malawi is declared COVID-19 free or further measures have been put in place to protect patients at this clinic. Therefore, the following formula has been used to calculate the sample size with reference to a similar study conducted by

Awotidebe et al. (2016) in Nigeria and the trend of cardiac patients attending the chest clinic at QECH;

$$n = \frac{[(Z_{\alpha} + Z_{\beta}) \times 2(\sigma)^2]}{(\mu_1 - \mu_2)^2}$$

Where  $\mu_1$ =mean in group 1,  $\mu_2$ =mean in group 2,  $Z_{\alpha}=0.9$ ,  $Z_{\beta}=0.84$  (power),  $\sigma=1.2$

The sample size for this study is based on detecting the effect size (the difference between the groups) of 0.6 at 80% power with a two-tailed significance level of 0.05. Using the formula above, a total sample size of 40 was obtained for each group. Owing the attrition of dropout rates of 5%, the sample size required is 80 (40 on each arm). To avoid issues of bias in participant selection, all patients will be selected from the chest clinic at the hospital. According to the chest clinic records, both sexes and different adult age groups (usually 45 years and above) are presented on each clinic day. Numbers 1 and 2 will be put on small pieces of paper, which will be placed in sealed and unmarked brown envelopes. Each participant will be asked to pick one envelop that will determine to which group she or he will belong to; this will assist in avoiding the selection bias. In addition, to ensure that the sample size is reached, discussions will be done with the head of the chest clinic to schedule more patients with CCF within the study participants' enrolment period. According to the available recommendations worldwide, 10 patients are allowed to exercise using a circuit training approach for an hour, and 3-4 therapists must be available to supervise the program to ensure safety. Because access to the Physiotherapy department at QECH to implement this pilot intervention is in the afternoon (13:00-12:00pm), and the number of patients enrolled into the active Arm is 40, the College of Medicine Physiotherapy gym will be used; and therapy session will be every Wednesday from 8:30 am to 12:30 pm. Nevertheless, the Physiotherapy department at QECH will be actively involved in the care delivery of these patients at College of Medicine Physiotherapy gym throughout the study, for capacity building and to ensure continuity of care after the implementation of this study. The participants shall be recruited over a period of two months.

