### ***Specific Objectives:***

1. To describe improvements in cardiovascular function at rest and on exercise among patients with a diagnosis of CHF
2. To describe the frequency of hospitalization among patients diagnosed with CHF enrolled into the cardiovascular rehabilitation program (CRP).
3. To describe the challenges that may be associated with establishment of a CRP at the QECH.

**Study design, population, sample size and sampling strategy:** This will be a prospective open label clinical trial of patients being discharged from the medical wards at QECH with a diagnosis of CHF. There will be two arms in the study with a total of 80 participants; Arm 1 will comprise of 40 patients with CHF who will receive cardiovascular rehabilitation as an intervention of interest, along with the usual cardiac medications that also include secondary prevention drugs, while 40 patients with CHF in arm 2 will be on cardiac medications that also include secondary prevention medications and education but not the exercise component of cardiac rehabilitation. Each participant will pick unlabelled sealed envelope with a paper that has a number that will determine to which group he or she will belong to. Participants will be followed up for 24 weeks. Participants in arm 1 will have regular cardiovascular exercise training once a week for 12 weeks and followed up without active exercise training for another 12 weeks. Arm 2 participants shall receive education component of cardiac rehabilitation at baseline and during the time points they will come for screening. Participants in both arms 1 and 2 will

continue to take cardiac medications as per their cardiologist's prescription throughout the study period.

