## **6.0 Analysis and presentation of results**

The SPSS software will be used to analyze this data. Frequencies and mean changes with standard deviations will be used to descriptively illustrate the effect size of the intervention. Paired t-tests will be carried out to compare and show the changes in the variables at the start of the program and after 3 and 6 months of CR reception. **Independent t-tests will be carried out to compare results between the two groups.** Tables and graphs will be used to present the findings.

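### The sample-size calculation in section 4.4 does not give 40 per arm; on its own inputs 40 per arm has about 60% power (58% after dropout), not the stated 80%

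*Protocol*

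**What the plan says.** Protocol section 4.4 prints a formula for comparing two means. The numerator is the sum of Zα and Zβ multiplied by 2σ², and the denominator is the squared difference in means. The sum carries no square. The values listed beneath it are Zα = 0.9, Zβ = 0.84 and σ = 1.2.

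The text then gives the target as "detecting the effect size (the difference between the groups) of 0.6 at 80% power", "with a two-tailed significance level of 0.05". It reports the result as "Using the formula above, a total sample size of 40 was obtained for each group", and continues: "Owing the attrition of dropout rates of 5%, the sample size required is 80 (40 on each arm".

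The Executive summary repeats the total ("There will be two arms in the study with a total of 80 participants") without any power statement. Section 6.0 names the between-group test: "Independent t-tests will be carried out to compare results between the two groups". Section 4.4 refers to a similar trial in heart failure (reference 25) and to clinic attendance as the basis for the calculation. It does not say which outcome, or which unit, 0.6 and 1.2 belong to.

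**The concern.** Four things in the calculation do not fit together:

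- The sum of the deviates is not squared, as the two-means formula requires.
- Zα = 0.9 does not match the stated two-sided 5% level, which needs 1.96. A deviate of 0.9 corresponds to a two-sided level of about 0.37.
- The result of 40 does not follow from the printed formula and values.
- The number per arm is the same before and after the dropout allowance.

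This calculation is the only formal basis given for the size of the trial, and it carries an explicit 80% power claim. If true power is nearer 58 to 60%, the trial would miss the planned difference about four times in ten. A non-significant comparison could then be given more weight as evidence against rehabilitation than it deserves. Because no outcome is attached to the figures, a reader cannot judge whether 0.6 is a meaningful difference in any of the measures collected (blood pressure, heart rate, oxygen saturation, exercise capacity, admissions).

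**Working it through.** **Inputs, all from section 4.4:** difference 0.6; σ = 1.2; Zα = 0.9 as printed (1.96 for two-sided 0.05); Zβ = 0.84 (80% power); dropout 5%; 40 per arm. The test is the independent t-test of section 6.0. The common factor is 2σ²/(difference)² = 2 × 1.44 / 0.36 = 8.

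**Step 1. Trying to reproduce 40.**

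| Version | Calculation | Per arm, rounded up |
|---|---|---|
| As printed | (0.9 + 0.84) × 8 = 13.9 | 14 |
| Sum squared, Zα = 0.9 | 1.74² × 8 = 24.2 | 25 |
| Unsquared, Zα = 1.96 | 2.80 × 8 = 22.4 | 23 |
| Correct: squared, Zα = 1.96 | 2.80² × 8 = 62.7 | 63 (64 by t-test) |
| One-sided 0.05, squared | normal formula | 50 |

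The only setting that comes near 40 is a one-sided 0.10 level (two-sided 0.20), which gives 37, or 39 after 5% dropout. That contradicts the stated level. No version consistent with two-sided 0.05 gives 40.

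**Step 2. Dropout.** Inflating 40 for 5% loss gives 40/0.95 = 42.1, so 43 per arm. Put the other way, enrolling 40 leaves 40 × 0.95 = 38 evaluable.

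**Step 3. Power actually available** (two-sample t-test, two-sided 0.05).

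| Reading of 0.6 | 40 per arm | 38 per arm | Needed for 80% |
|---|---|---|---|
| Raw difference, SD 1.2 (0.5 SD) | 59.8% | 57.6% | 63–64 |
| Standardised effect of 0.6 | 75.5% | 73.3% | 44–45 |

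For the standardised reading, the normal formula is 2 × 2.80² / 0.36 = 43.6, so 44; the t-test needs 45. With 5% dropout, the raw-difference reading needs 67 to 68 enrolled per arm (63/0.95 = 66.3; 64/0.95 = 67.4).

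**Step 4. What 38 evaluable per arm can detect.** At 80% power the detectable effect is 0.651 SD, and 0.651 × 1.2 = 0.78 on the plan's scale, against the planned 0.6.

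**The case against.** **The reading of 0.6.** Section 4.4 calls 0.6 an effect size and, in the same phrase, the difference between groups, so a standardised effect may have been intended. Power would then be 73 to 75% and the miss rate about one in four. This moderates the size of the shortfall but does not remove it. The raw reading also has better support: 0.6 is described as a between-group difference, and the formula pairs it with σ, which would have no role otherwise.

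**A pilot.** The study is called a pilot, its specific objectives are worded as descriptive, and clinic numbers also shaped its size. That is a sound reason not to demand more patients. It does not excuse the power statement, because the protocol makes a formal 80% claim, plans t-tests between arms, and expects better function and fewer admissions in the exercise arm. How a null result would be read is a prediction, not a certainty.

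**Lost formatting.** The missing square could be a superscript lost when the PDF was read. Restoring it gives 25 with 0.9 and 63 with 1.96, so 40 is still not reached. A lost superscript also cannot account for Zα = 0.9 or the missing dropout allowance.

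**A cited source.** The inputs may come from the trial in reference 25, which is not available here. That could show where 0.6 and 1.2 come from; it would not make the arithmetic work.

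**Conclusion.** The concern holds. The formula and its Zα are wrong for the stated design, 40 per arm does not follow from them, and the 5% dropout is not applied. Taking 0.6 as a raw difference with SD 1.2, as the section presents it, power is 60% with 40 per arm and 58% with 38, and the stated 80% would need 63 to 64 evaluable per arm. Taking 0.6 as a standardised effect, power is 75% and 73%. The 80% claim fails on either reading. The figures assume 1:1 allocation, a two-sided 5% t-test and exactly 5% loss in each arm. As the only formal justification of the trial's size, the calculation must be corrected.

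**What to change.** Correct section 4.4 as follows:

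- Print n per arm = 2σ²(Zα/2 + Zβ)² / (difference)², with Zα/2 = 1.96 and Zβ = 0.84.
- Keep 80 patients and state what they provide after 5% dropout (38 evaluable per arm): about 58% power for a difference of 0.6 with SD 1.2, or 80% power for a difference of 0.78 (0.65 SD).
- Name the outcome, time point and unit that 0.6 and 1.2 refer to, and say whether 1.2 is the SD of a single follow-up measurement or of the change from baseline. If 0.6 is a standardised effect, say so, remove σ = 1.2 and report 73% power with 38 per arm.

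A baseline-adjusted comparison could recover some power, but how much depends on which SD 1.2 is. With 38 per arm and a baseline correlation of about 0.65, power returns to about 80% if 1.2 is the SD of a follow-up score. If it is the SD of change, power reaches only about 66%. If this route is taken, the assumed correlation and the type of SD should be stated.

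The cost is wording in section 4.4 and a less favourable power statement. No extra patients are needed. The Executive summary gives only the total of 80 and can stand. Delivering the original 80% for 0.6 would instead mean enrolling 67 to 68 per arm (134 to 136 in total), which looks unrealistic given the 5 and 13 eligible-diagnosis patients that section 4.4 reports for the two most recent clinic months.

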#### **4.5 Intervention and implementation procedure**

Patients will be referred for CR from the medical team in the chest clinic; the referral shall be based on the inclusion and exclusion criteria. The referring of patients for screening and enrolment shall be terminated after the eight-week period. All patients will be screened again for CR eligibility using the set inclusion and exclusion criteria; following which a thorough assessment will be conducted for each patient (Appendix 10) . Briefly, the following parameters will be recorded for each patient; demographic data, medical and social history (including medications and dosages), resting Blood Pressure (BP), Pulse Rate (PR), Respiratory Rate (RR), Body Weight (BWT), Height (H), Body Mass Index (BMI) and exercise capacity.

Furthermore, risk stratification will be conducted to ascertain the risk for cardiac events during the exercise therapy; although the low-moderate risk category of patients will be offered close supervision to ensure safe exertion, all high risk patients will be excluded from exerting. In addition, each patient will be risk stratified for disease progression, to ascertain availability of risk factors and the risk for rapid progression of the disease; this will assist the therapists to plan and deliver an effective education and counselling intervention to influence life style modification. Thereafter, exercise tolerance test will be conducted using 6-minute walk test; this will assist therapists to prescribe the appropriate and safe target exertion zone at which each patient must exercise to gain positive results.

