#### **4.6 SAFETY CONSIDERATIONS**

As mentioned in section 4.5, all patients will be risk stratified for risk of cardiac events during exercise therapy. The risk stratification checklist is attached as an appendix (1) to this document. All patients classified as high risk will be excluded from participation in the study. In addition, only CR trained and registered Physiotherapists will be employed to administer the CR intervention to these patients. Furthermore, all patients will be assessed (BP, PR and general wellbeing) before and after each exercise therapy session to ensure that they are safe to exert and to exit the clinic soon after the therapy session respectively. Additionally, the study will only enroll patients who are also on secondary prevention medications; and therapists will ensure that all enrolled participants are adhering to their medications on each session day. Finally, one guardian for each patient will be trained on how they can supervise a prescribed home exercise program to ensure that patients exert safely at home. In case an adverse event such as syncope, cardiac arrest or sudden death has been recorded amongst the study population within 24 hours of exercise therapy, a proper documentation will be done and the case will be thorough investigated to ascertain if exercise therapy is indeed the cause. This and all proceedings of the investigations will also be reported to COMREC immediately in writing. In a situation where the causation is ascertained and exercise therapy is found to be at fault, the intervention will be terminated.

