| 
 
• Left ventricular ejection fraction > 50%
 
• No resting or exercise-induced complex dysrhythmias
 
• Uncomplicated MI, CABG, angioplasty, atherectomy, or stent:
 
• Absence of CHF or signs/symptoms indicating post-event ischemia
 
• Normal hemodynamic and ECG responses with exercise and in recovery
 
• Asymptomatic with exercise or in recovery, including absence of angina
 
• Maximal functional capacity at least 7.0 METs*
 
• Absence of clinical depression or depressive symptoms
 
 | 
 
• Patients neither meet High Risk nor Low Risk standards;
 
• Left ventricular ejection fraction = 40–50%
 
• Signs/symptoms including angina at “moderate” levels of exercise (60–75% of maximal functional capacity) or in recovery
 
• Mild to moderate silent ischemia (ST depression less than 2mm) with exercise or in recovery
 
 | 
 
• Left ventricular ejection fraction < 40%
 
• Survivor of cardiac arrest or sudden death 
 
• Complex ventricular dysrhythmias (ventricular tachycardia, frequent [> 6/min] multiform PVCs) at rest or with exercise
 
 
 
• MI or cardiac surgery complicated by cardiogenic shock, CHF, and/or signs/symptoms of post-procedure ischemia
 
• Abnormal hemodynamics with exercise, especially flat or decreasing systolic blood pressure or chronotropic incompetence with increasing workload
 
• Significant silent ischemia (ST depression 2mm or greater without symptoms) with exercise or in recovery
 
• Signs/symptoms including angina pectoris, dizziness, lightheadedness or dyspnea at low levels of exercise (< 5.0 METs) or in recovery
 
• Maximal functional capacity less than 5.0 METs*
 
 |

|  |  |                                                                                                            |
|--|--|------------------------------------------------------------------------------------------------------------|
|  |  | 

• Clinically significant depression or depressive symptoms

 |
|--|--|------------------------------------------------------------------------------------------------------------|

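### Allocation by a free pick from unmarked envelopes leaves no checkable record, and the protocol does not settle the high-risk exclusion or its timing relative to the pick

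*Protocol*

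**What the plan says.** **Allocation.** Section 4.4 describes the material: "Numbers 1 and 2 will be put on small pieces of paper, which will be placed in sealed and unmarked brown envelopes". It then describes the act: "Each participant will be asked to pick one envelop that will determine to which group she or he will belong to". The executive summary gives the same method: "Each participant will pick unlabelled sealed envelope with a paper that has a number". Section 4.4 presents the pick as a way of avoiding selection bias and plans 40 patients per arm. The design is open label (executive summary and section 4.1).

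**High-risk patients.** Being classed as high risk for cardiac events on exertion is exclusion criterion (e) in section 4.32. Section 4.6 agrees: "All patients classified as high risk will be excluded from participation in the study". Section 4.5 words the consequence differently: "all high risk patients will be excluded from exerting".

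**Order of steps.** Section 4.5 runs from eligibility screening to assessment, then to the two risk stratifications, and then continues: "Thereafter, exercise tolerance test will be conducted using 6-minute walk test". The assessment that comes before stratification also lists exercise capacity among its parameters. Section 4.7 places screening before enrolment into the programme and names the Chester step test as the basis for prescription. Among the high-risk items in Appendix 1 is "Maximal functional capacity less than 5.0 METs".

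**The concern.** Sealing an envelope hides its content until it is opened. It does not bind a particular envelope to a particular patient. Protection from selection bias also requires that the assignment be fixed in advance and that any departure from it show up. With a free pick from unmarked envelopes, staff who know the arms could allow a second pick, put an envelope back or exchange slips, and no record would reveal it. Nobody could later show that the assignments were sound, which weakens every between-group comparison in section 6.0.

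The second issue is when final eligibility is settled. If a high-risk class can emerge after the pick, what follows depends on which section is applied. Under section 4.5 the consequence concerns exercise, and supervised exercise is given only in Arm 1. Losing the least fit patients mainly from that arm would favour rehabilitation on walk distance and admissions.

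**Working it through.** **1. What the allocation text fixes.** Executive summary and section 4.4 taken together:

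| Element | Stated? |
|---|---|
| Slips marked 1 or 2, sealed envelopes | Yes |
| Number of envelopes of each kind | No |
| Whether a used envelope is replaced | No |
| Pre-set sequence or envelope numbers | No |
| Patient ID on the envelope, opening log, custodian | No |
| Timing of the pick relative to tests and final eligibility | No |

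The executive summary and section 4.4 agree with each other, and neither allows an assignment to be checked.

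**2. Is 40:40 secured?** The plan's figure is 80 patients, 40 per arm. The protocol does not say which scheme applies, so each result below is conditional.

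- *40 + 40 envelopes, no replacement, all 80 drawn:* exactly 40:40, with certainty.
- *40 + 40 envelopes, no replacement, recruitment stops early:* section 4.4 reports 5 and 13 heart-failure patients in the two months after the clinic reopened, so 5 + 13 = 18. If recruitment stopped there (an assumption), the number in Arm 1 would be Hypergeometric(80, 40, 18), and P(12:6 or more uneven) = 18.0%. The loss of precision would be modest: (1/12 + 1/6) / (1/9 + 1/9) = 0.250 / 0.222 = 1.125, and √1.125 = 1.06, so the standard error rises by about 6%.
- *Envelopes reused (an assumption):* the number in Arm 1 would be Binomial(80, 0.5). Then P(exactly 40:40) = 8.9%, P(45:35 or more uneven) = 31.4% and P(more than 40 in Arm 1) = 45.6%. The last figure matters because the session plan in section 4.4 (10 patients per hour, 8:30 to 12:30) holds 4 × 10 = 40.

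These figures describe chance imbalance. They do not measure selection bias.

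**3. The high-risk class.**

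| Question | Place | Content |
|---|---|---|
| Consequence of high risk | 4.32 (e), 4.6 | Not in the study |
| Consequence of high risk | 4.5 | Not to exercise |
| Exercise result available before stratification? | 4.5, assessment | Exercise capacity is listed, so perhaps yes |
| Exercise result available before stratification? | 4.5, next paragraph | Walk test comes after stratification, so no |
| Do high-risk items need exercise results? | Appendix 1 | Some do (METs, haemodynamics with exercise, silent ischaemia with exercise); others do not (ejection fraction, survived cardiac arrest, depression) |
| Where are METs recorded? | Step-test form; Appendix 3 | On the step-test form; the walk-test form has no METs field |
| Is either test certain at baseline? | Appendix 10 | The form treats both as optional |

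The order is inconsistent rather than plainly wrong. A patient whose only high-risk feature is exercise-based could be classified before that feature is measured.

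**4. What Arm 1-only removal would do, if it happened.** This is an illustration, and both the share removed and the correlation are assumed. Remove the lowest share x of Arm 1 by exercise capacity, with correlation r between capacity and outcome. With c = Φ⁻¹(x), the bias is r·φ(c)/(1 − x) in SD units, and SE = √[1/(40(1 − x)) + 1/40]. The last column is the chance of a significant difference with no true effect, at a nominal 5%.

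| x | SE | Bias, r = 0.3 to 0.5 | Type I error, r = 0.3 to 0.5 |
|---|---|---|---|
| 5% | 0.227 | 0.03 to 0.05 SD | 5.2% to 5.7% |
| 10% | 0.230 | 0.06 to 0.10 SD | 5.7% to 7.1% |
| 20% | 0.237 | 0.10 to 0.17 SD | 7.3% to 11.4% |
| 30% | 0.246 | 0.15 to 0.25 SD | 9.3% to 17.2% |

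**The case against.** Three objections have force.

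*The exclusion applies to both arms.* A reader might infer that high-risk exclusions will fall on Arm 1 alone. The protocol does not say so. High risk is a study exclusion criterion, section 4.6 repeats it, section 4.5 screens all patients, and section 4.7 puts screening before enrolment into the programme. The Arm 1 scenario needs an unstated timing of the pick, and the section 4.5 wording to override two other sections. It is a possibility left open, and no more. The table in step 4 of the working is no estimate for this trial.

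*The step test is not tied to an arm.* A reader might infer from its prescription purpose that only Arm 1 performs it. Section 4.7 names no arm, and the Appendix 10 baseline form provides for it in any patient, so that inference is unsupported.

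*40 + 40 envelopes is the natural reading.* With 40 per arm fixed, the natural scheme is to prepare 40 of each, and balance is then guaranteed at 80. The 31.4% and 45.6% figures need reuse, which is nowhere stated. The 18-patient case ignores the intention in section 4.4 to schedule more patients with heart failure. None of these figures should be read as expected behaviour.

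None of this answers the main point. Even with 40 + 40 envelopes, a free pick from unmarked stock cannot be audited.

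**Conclusion.** The allocation point holds on the text alone and needs no numerical assumption: the method is described twice, consistently, and does not deliver the protection claimed for it. It shows an unguarded route to selection bias, not that bias will occur, and its size cannot be derived from the protocol. Balance at 40:40 holds only under the two conditions given in the working: no replacement and a complete draw.

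The contradiction over high-risk patients also holds as an inconsistency to be resolved. A differential loss from Arm 1 is neither stated nor excluded. Overall this is a change that should be made before enrolment, and it is easily made.

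**What to change.** **Allocation.** Replace the free pick with a computer-generated list using randomly varied, undisclosed block sizes, prepared by someone outside recruitment. Fixed blocks would be partly predictable in a single-site, open-label trial. Place the assignments in sequentially numbered, opaque, sealed envelopes. Open them strictly in order, writing the patient ID and date on each envelope first, and only after consent, baseline measures and final eligibility (including the Appendix 1 risk class) have been recorded. Keep the opened envelopes and a log. Analyse every patient in the allocated arm, including anyone reclassified later.

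**Eligibility.** The clinical team should reconcile sections 4.32, 4.5, 4.6 and 4.7 with Appendix 1 on what a high-risk class entails and where exercise testing sits relative to it. Those are clinical decisions and none is proposed here. The statistical requirement is that the same eligibility determination be completed for all patients before allocation, and that the protocol state when the envelope is opened.

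**Cost.** A printed list, numbered envelopes and a re-ordered baseline visit.
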